## Abstract

**Objectives::**

To investigate the effect of tDCS on the performance of children and adolescents with ADHD in the neuropsychological tests of visual attention, verbal, and inhibitory control.

**Methodology::**

Triple blind, randomized, sham-controlled, cross-over trial involving tDCS in children and adolescents with ADHD. Initial screening will be performed using Swanson, Nolan, and Pelham – IVand Wechsler intelligence scale for children fourth edition vocabulary and cube subtests. Individuals will be evaluated pre-tDCS and post-tDCS with the Wechsler intelligence scale for children fourth edition Digitus subtest, neuropsychological assessment battery second edition inhibiting responses subtest, Corsi cubes, and visual attention test-4.

## Introduction

1

Attention-deficit/hyperactivity disorder (ADHD) is a prevalent developmental disorder characterized by inadequate levels of attention, hyperactivity and impulsivity and frequently comorbid with other psychiatric disorders.^[1]^ According to the American Academy of Pediatrics, different areas of the child's life may be compromised as a result of ADHD, such as academic performance, interpersonal relationships and well-being, raising the need for effective treatments.^[1,2]^ The main current therapeutic strategies recommended and widely used are based in psychostimulants and behavioral therapies. They have proven efficacious and cost-effective in the short term,^[1]^ however, there have been reports in the literature of adverse effects in children and adolescents with the use of some of these medications, among them tachyphylaxis, increased blood pressure and heart rate, insomnia, and reduced appetite.^[3–6]^

Some studies report a relationship between ADHD symptoms and executive function deficits.^[7]^ The central executive functions are cognitive flexibility, inhibitory control (self-control and self-regulation), and working memory. The most complex executive functions include problem solving, reasoning, and planning.^[8]^ Inhibitory control, the ability to inhibit prepotent actions, is altered in children and adults with ADHD.^[9]^ It has been suggested that repetitive transcranial magnetic stimulation and transcranial direct current stimulation (tDCS) on the dorsolateral prefrontal cortex could improve inhibitory control, impulsivity, and decision-making.^[10]^

In the past decades, several interventions and diagnostic tools have been tested for brain and mind disorders.^[11–23]^ Among them, tDCS is an emerging neuromodulation technique that uses low-intensity electrical stimulation to modulate target brain regions and has a potential therapeutic benefit because the neurophysiological effect of current applied is durable over time after the stimulation ceases.^[24]^ The anodic tDCS is based on an electric current from a generator that aims to stimulate certain cortical areas, causing an increase in local cerebral blood flow.^[25]^ This tool has been currently used in the treatment of various psychiatric and neurological disorders such as schizophrenia,^[26]^ dyslexia,^[27]^ autism,^[28]^ cerebellar ataxia,^[29]^ epilepsy,^[30]^ unipolar and bipolar depression,^[31]^ since it is considered safe and relatively less expensive than other noninvasive brain stimulation approaches.^[32,33]^ Advantages of the cost-effectiveness of tDCS could be even more important considering low-middle income countries.^[34,35]^

Previous studies have shown that tDCS is both a safe and an encouraging option in the treatment of ADHD,^[10,36–40]^ proving the validity of researching this method and its adverse effects. In addition, some children and adolescents present contraindications for the use of psychoactive drugs, necessitating the use of alternative methods. The pilot open-label trial conducted by Bandeira et al^[38]^ showed improvement in some executive functions such as selective attention and inhibitory control using tDCS in children and adolescents with ADHD. However, further studies with appropriate randomization, blinding, and larger sample sizes should be performed to further investigate these findings. The main objective of this study is to widen the scope of the previous investigation and to prove reproducibility of the findings as well as ensure safety of the technique in this population.

## Study aims

2

### Principal

2.1

To determine the impact of tDCS on attention and inhibitory control in children and adolescents with ADHD.

### Secondary

2.2

To identify the adverse effects related to tDCS in children and adolescents with ADHD.

## Material and methods

3

### Study design

3.1

This is a randomized, crossover, triple-blind, sham-controlled study. The study was registered on December 28th, 2017 with Brazilian Registry of Clinical Trials (ReBec) as “The Effects of Transcranial Direct Current Stimulation on Attention and Inhibitory Control of Children and Adolescents with Attention-Deficit/Hyperactivity Disorder (ADHD): a randomized, sham-controlled, triple blind, cross-over trial” (http://www.ensaiosclinicos.gov.br/rg/RBR-7h5qzf/).

### Participants and enrollment

3.2

#### Casuistry

3.2.1

The sample will consist of 15 individuals of both genders from the Attention Deficit Hyperactivity Disorder Outpatient Clinic of the [name] University Hospital, Federal University of Bahia without pharmacological treatment during tDCS intervention.

#### Definitive diagnostic criteria

3.2.2

The diagnosis of ADHD will be performed by neuropediatricians based on the criteria of the 5th edition of the diagnostic and statistical manual of mental disorders (DSM-5).

### Eligibility criteria

3.3

#### Inclusion criteria

3.3.1

(1)Individuals aged between 6 and 16;(2)Diagnosed with ADHD according to DSM-5 criteria;(3)Absence of psychiatric comorbidities;(4)Right handed;(5)Literate and enrolled in regular schools;(6)Living in Salvador (Brazil) or metropolitan area;(7)No pharmacological treatment during tDCS intervention;(8)Electroencephalogram without epileptogenic activity;(9)Consent of those responsible for participation in the study.

#### Exclusion criteria:

3.3.2

(1)Sensory deficit.(2)Not conforming to any of the above criteria

### Sample calculation

3.4

The sample size calculation was performed based on a pilot study. We used the variable “errors by default” of visual attention test (TAVIS) test as the primary outcome. Considering the level of significance of 5%, the power of 80%, the mean difference between paired groups of 1.2 and the standard deviation of 1.24, the sample size calculation resulted in 11 subjects. Assuming 25% of dropout, our final sample size was 14 subjects.

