### Interventions

3.8

After selecting the sample according to the aforementioned criteria and neuropediatric evaluation, children diagnosed with ADHD will participate in a neuropsychological assessment in which the intellectual level estimation and its performance in the processes of attention, operational memory, and inhibitory control will be investigated. The Swanson, Nolan, and Pelham – IV questionnaire assessing the diagnostic criteria for ADHD from the DSM-5 will be applied to the parents.

A total of 15 individuals will be selected, randomly assigned in 2 groups, 8 of whom were initially in the tDCS group and 7 in the sham group. It will be made clear to those responsible and to the relevant child that tDCS may not be applied. During the stimulation, the same conditions will be reproduced in both groups, except for active treatment in the sham group. The patient will be informed about the procedure before the beginning of the study, with the device being used for a first perception of the current flow for a few seconds.

The tDCS consists of an application of a direct electric current of low amplitude (2 mA) for 30 minutes from 2 electrodes (5 cm × 7 cm) embedded in saline solution. The anode will be positioned in the left anterior dorsal prefrontal cortex (F3 according to the electroencephalogram system 10–20) and the cathode in the supraorbital region on the opposite side. The device used will be the Striat (Ibramed, Amparo-SP, Brazil), approved by the Brazilian National Health Agency (ANVISA). During the stimulation period participants will participate in playful activities involving memory and attention, such as the “Super Lynx” and “Genius” games. They will be carried out by an appropriately trained individual, in 5 sessions, 1 per day, and in the presence of a physician trained to deal with possible intercurrences. Participants may withdraw from participating in the study at any time according to the informed consent form.

After 1 month, the groups will be crossed. Thus the 8 children initially stimulated will be part of the sham group in the second phase and the children initially in the sham group will then receive active stimulation. Before and after the new cycle of stimulation, neuropsychological evaluations will be carried out by applying the aforementioned tests. The family, the research subject, the evaluators, and the statistician will be blind to the subject's group.

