
### Statistical analyses

3.10

To test the hypotheses of the study various inferential statistical tests will be performed with a comparison of means and medians (Student *t* test and Wilcoxon) using the SPSS statistical package for Windows. In the inferences, a significant result will be considered if the probability of type I error is ≤0.05 (5%).

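### The 25% dropout allowance on 11 children gives 15, not the 14 stated in section 3.4, and 14 conflicts with the 15 planned in sections 3.2.1 and 3.8

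*Protocol article*

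**What the plan says.** Section 3.4 (Sample calculation) bases the size on a paired comparison of a visual attention test error count, with inputs from a pilot study: "the mean difference between paired groups of 1.2 and the standard deviation of 1.24", at 5% significance and 80% power. From these, "the sample size calculation resulted in 11 subjects". The section then allows for losses: "Assuming 25% of dropout, our final sample size was 14 subjects".

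Two other sections give a different total. Section 3.2.1 (Casuistry): "The sample will consist of 15 individuals of both genders". Section 3.8 (Interventions): "A total of 15 individuals will be selected, randomly assigned in 2 groups", with 8 children starting on active stimulation and 7 on sham. The article does not explain how 14 and 15 relate.

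**The concern.** There are two linked problems.

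- **Arithmetic.** A dropout rate is a share of the children enrolled, so the evaluable number must be divided by one minus that rate. Multiplying by one plus the rate gives too few. From 11 and 25%, division gives 15 and multiplication gives the printed 14.
- **Consistency.** Section 3.4 presents 14 as the final size, while sections 3.2.1 and 3.8 plan 15.

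Anyone who took section 3.4 as the recruitment target would stop one child short of what the plan's own dropout assumption requires, and would fall slightly below the stated power. Even if 15 are enrolled, the written justification does not support that number.

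**Working it through.** **Inputs, all from section 3.4:** mean paired difference 1.2; standard deviation 1.24; significance level 5%; power 80%; evaluable number 11; dropout 25%; final size 14. Planned enrolment of 15 is from sections 3.2.1 and 3.8.

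**Assumptions:** 1.24 is the standard deviation of the within-child differences, and the test is two-sided. The article states neither outright, but together they reproduce its 11.

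**Step 1: reproduce the 11.** The standardised effect is 1.2/1.24 = 0.968. Power of the paired t test comes from the noncentral t distribution with n − 1 degrees of freedom and noncentrality 0.968 × √n:

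| Completers | Power, two-sided 5% |
|---|---|
| 10 | 77.7% |
| 11 | 82.4% |

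The smallest number reaching 80% is 11, as stated. A two-sided normal approximation gives 8.4, or 9 children; with the usual small-sample term it gives 10.3, or 11. A one-sided t test would need only 9. The base figure is therefore sound.

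**Step 2: the dropout allowance.**

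- Multiplying: 11 × (1 + 0.25) = 13.75, rounded up to 14. This is the printed figure.
- Dividing: 11/(1 − 0.25) = 14.67, rounded up to 15.

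**Step 3: check each total against the requirement.**

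- 14 × 0.75 = 10.5 expected completers, below 11.
- 15 × 0.75 = 11.25 expected completers, above 11.

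**Step 4: the size of the effect.** Let each child drop out independently with probability 0.25, so that the number of completers is binomial. Average the paired t test power over that distribution:

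| Enrolled | Chance of at least 11 completers | Power averaged over dropout |
|---|---|---|
| 14 | 52.1% | 78.9% |
| 15 | 68.6% | 82.2% |

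The difference in averaged power is 82.2 − 78.9 = 3.3 percentage points. With 14 the shortfall from 80% is 80 − 78.9 = 1.1 points.

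**Step 5: compare the sections.** Section 3.4 ends at 14. Section 3.2.1 says 15. Section 3.8 says 15, and its 8 and 7 add to 15. The correctly inflated figure agrees with sections 3.2.1 and 3.8.

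**The case against.** The strongest reply is that nothing follows in practice. The sections that describe who will be enrolled both say 15, which is the correctly inflated number, and a calculated minimum of 14 can coexist with a plan to enrol 15. This stands as far as it goes: the trial as described is not undersized on this point.

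A second reply is that the article gives no formula, so the origin of 14 is inferred. The unrounded requirement for 80% power is 10.46, and 10.46/0.75 = 13.95, which also rounds up to 14 by the correct method. That route is possible, but section 3.4 states 11 children and then applies the dropout rate, and from 11 the division gives 15. The route also leaves the conflict with 15 untouched.

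A third reply is that power evaluated at 10.5 completers is 80.2%, so 14 does not miss the target. But 10.5 children cannot complete a trial. Averaged over the whole numbers that can occur, power with 14 is 78.9%. It is fair to add that this shortfall is about one point, on a calculation that rests on pilot values, and that even 15 enrolled would leave fewer than 11 completers about 31% of the time (100 − 68.6 = 31.4).

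**Conclusion.** The point holds: section 3.4 is wrong as written. From its own 11 completers and 25% dropout the number to enrol is 15, and the stated 14 also disagrees with the 15 in sections 3.2.1 and 3.8. That 14 arose from multiplying by 1.25 is the most natural reading, not something the article documents.

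The size is one child and about 3 points of power, enough to move dropout-averaged power from just above the stated 80% to just below it. The power figures rest on the two assumptions stated with the calculation and on independent dropout at 25% of those enrolled. The disagreement between 14 and 15 rests on no assumption. Because 15 is already planned, the defect lies in the stated justification and not in the planned recruitment. It should still be corrected, since the trial needs one target size.

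**What to change.** In section 3.4, replace the final sentence with one stating that, allowing for 25% dropout, 11/(1 − 0.25) = 14.7 is rounded up to 15 subjects. Sections 3.2.1 and 3.8, including the 8 and 7 allocation, then agree with it and need no change.

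The cost is one sentence. No extra children are recruited, and neither the design nor the analysis changes.

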### Randomization

3.5

The individuals participating in the study will be allocated to the sham group, which will not receive effective stimulation, and to the active group, in which tDCS will actually be performed. The allocation will be made randomly by an individual not involved with the study using the instrument available on randomization.com. A list with the allocation will be sealed in an opaque envelope, retained by one of the study authors and only opened on the first day of stimulation, by the same individual. Only the researchers who apply tDCS will have access to this information. After the defined interval of 1-month the individuals who underwent tDCS will be moved to the sham group and vice-versa.

### Blinding

3.6

The tDCS devices will be covered during the procedure and no patient or relative will have contact with them. To certify blinding of participants in the sham group in relation to the sensation of current flow involved in the procedure, the device will be switched on for 1 minute at the beginning of the stimulation, turned off for the subsequent 28 minutes and reconnected at the last minute of stimulation. The family, the research subject, the evaluators, and the statistician will be blind to the group to which the subject belongs (“Sham” or “Active”). At the end of the 5 tDCS or sham-tDCS sessions in the first stage of the study, patients and their families will be asked if they believed they were in the intervention or control group. After the 30 day washout period, the second stage of the study will be carried out in the same manner, with the same questioning at the end of the 5 sessions of tDCS or sham-tDCS.

### Variables

3.7

(1)Sex: 0-female; 1-male; 9-not declared;(2)Age, in years and months;(3)Grade level;(4)School: 0-public; 1-private;(5)Age of diagnosis of ADHD;(6)Use of medication to treat ADHD: 0-yes; 1-no;(7)Repeated school years;(8)Age of school inclusion;(9)Monitoring by neuropediatrician: 0-yes; 1-no;(10)Education of the responsible adult: 0-no schooling; 1-elementary incomplete; 2- elementary completed; 3- high-school incomplete, 4-high-school completed; 5-college incomplete; 6-college completed; 7-postgraduate;(11)Intelligence Quotient;(12)Average basic reaction time to the TAVIS instrument;(13)Raw number of errors by omission using TAVIS;(14)Raw number of hits using TAVIS;(15)Raw score of vocabulary subtest with Wechsler abbreviated intelligence scale;(16)Raw score of forward order of digits with Wechsler intelligence scale for children fourth edition (WISC-IV);(17)Raw score of backward order of digits with WISC-IV;(18)Forward order hits using Corsi block;(19)Backward order hits using Corsi block;(20)Total errors with the inhibition subtest.

### Interventions

3.8

After selecting the sample according to the aforementioned criteria and neuropediatric evaluation, children diagnosed with ADHD will participate in a neuropsychological assessment in which the intellectual level estimation and its performance in the processes of attention, operational memory, and inhibitory control will be investigated. The Swanson, Nolan, and Pelham – IV questionnaire assessing the diagnostic criteria for ADHD from the DSM-5 will be applied to the parents.

A total of 15 individuals will be selected, randomly assigned in 2 groups, 8 of whom were initially in the tDCS group and 7 in the sham group. It will be made clear to those responsible and to the relevant child that tDCS may not be applied. During the stimulation, the same conditions will be reproduced in both groups, except for active treatment in the sham group. The patient will be informed about the procedure before the beginning of the study, with the device being used for a first perception of the current flow for a few seconds.

The tDCS consists of an application of a direct electric current of low amplitude (2 mA) for 30 minutes from 2 electrodes (5 cm × 7 cm) embedded in saline solution. The anode will be positioned in the left anterior dorsal prefrontal cortex (F3 according to the electroencephalogram system 10–20) and the cathode in the supraorbital region on the opposite side. The device used will be the Striat (Ibramed, Amparo-SP, Brazil), approved by the Brazilian National Health Agency (ANVISA). During the stimulation period participants will participate in playful activities involving memory and attention, such as the “Super Lynx” and “Genius” games. They will be carried out by an appropriately trained individual, in 5 sessions, 1 per day, and in the presence of a physician trained to deal with possible intercurrences. Participants may withdraw from participating in the study at any time according to the informed consent form.

After 1 month, the groups will be crossed. Thus the 8 children initially stimulated will be part of the sham group in the second phase and the children initially in the sham group will then receive active stimulation. Before and after the new cycle of stimulation, neuropsychological evaluations will be carried out by applying the aforementioned tests. The family, the research subject, the evaluators, and the statistician will be blind to the subject's group.

At the end of each session, participants and their families will be asked about the presence of the most prevalent adverse effects related to tDCS reported in previous studies.^[36,38,41]^ Any adverse event identified as severe by the attending physicians will be a criteria for exclusion from the study.

The participants will be contacted by telephone the day before the intervention to confirm their participation, thus avoiding possible absences. In order to promote participant retention and complete follow-up, it will be collected outcome data from participants who discontinue or deviate from intervention protocols. In addition, to promote data quality, the data values will be checked by 2 external individuals to avoid incorrect analysis.

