#### Neuropsychological evaluation

3.9.1

All participants will be evaluated by neuropsychological tests at 4 different moments: before the first cycle, with an intellectual screening and additional behavioral analysis; after the first cycle and before and after the second cycle. The tests will be applied by neuropsychologists with experience in the evaluation process and using the following instruments:

Characteristics of the sample:

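### A severe adverse event is written as grounds for removal from the study, when it should stop further stimulation and leave follow-up in place

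*Protocol article*

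**What the plan says.** All of the statements are in the protocol article.

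- Section 3.8, on severe events: "Any adverse event identified as severe by the attending physicians will be a criteria for exclusion from the study".
- The sentence just before it fixes the timing: "At the end of each session, participants and their families will be asked about the presence of the most prevalent adverse effects". Reports therefore arise once sessions have begun, after allocation.
- The next paragraph of section 3.8, on retention: "it will be collected outcome data from participants who discontinue or deviate from intervention protocols". Its stated purpose is to keep participants and complete their follow-up.
- Section 3.8, on voluntary departure: "Participants may withdraw from participating in the study at any time according to the informed consent form".
- Section 2.2, the secondary aim: "To identify the adverse effects related to tDCS in children and adolescents with ADHD".
- Section 3.9.1 places the four neuropsychological assessments before the first cycle and then "after the first cycle and before and after the second cycle".
- Section 3.1, on the design: "This is a randomized, crossover, triple-blind, sham-controlled study".

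**The concern.** Stopping stimulation after a severe event is right. The difficulty is that the sentence removes the child from the study as a whole. Two things are at stake.

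The first is safety follow-up. Adverse effects are the secondary aim. Staff who apply the sentence as written could stop seeing a child just when a severe event needs to be followed, and its later course could go unrecorded.

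The second is missing data that depend on an outcome. A rule triggered by an event that may be related to treatment makes the remaining assessments missing for a reason linked to treatment. The retention sentence appears intended to prevent this, but nothing states that it covers a child who meets the severe-event rule.

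**Working it through.** **1. The wording side by side.** Section 3.8 describes three ways in which a child's course may change:

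| Situation | What the child leaves | Data afterwards |
|---|---|---|
| Voluntary withdrawal | the study | not stated |
| Stopping or deviating from the intervention | the intervention | outcome data collected |
| Severe adverse event | the study | not stated |

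By its wording, the severe-event rule matches the first row. By its purpose and its position directly after the session-end questions, it could belong with the second. No sentence settles the matter.

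**2. Assessments at stake.** From the schedule in section 3.9.1: test 1 before cycle 1, test 2 after cycle 1, test 3 before cycle 2, test 4 after cycle 2.

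- Event during cycle 1: test 1 is done, so 4 − 1 = 3 are forgone under the literal reading.
- Event during cycle 2: tests 1 to 3 are done, so 4 − 3 = 1 is forgone.
- Under the retention sentence, or with the fix: 0 are forgone by rule.

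These are neuropsychological tests, not safety visits. Nor does continued testing always save the crossover comparison. A child stopped in cycle 1 has no second cycle of stimulation and gives no active-sham contrast whether or not the later tests are done. A child stopped in cycle 2 has begun both conditions, so test 4 keeps a within-child comparison, although after a shortened second course.

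**3. How many children.** The article gives no rate of severe events. As an assumption, take a per-child risk p among the 15 children of section 3.8. The expected number is 15p and the chance of at least one is 1 − (1 − p)^15.

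| Assumed p | Expected number | Chance of at least one |
|---|---|---|
| 1% | 0.15 | 14% |
| 2% | 0.30 | 26% |
| 5% | 0.75 | 54% |
| 10% | 1.5 | 79% |

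**4. Power, to show that it is not the issue.** Section 3.4 gives a paired difference of 1.2, a standard deviation of 1.24, a 5% level and 80% power, with 11 subjects as the result. The standardised difference is 1.2/1.24 = 0.968. A two-sided paired t test (two-sidedness is assumed), using the noncentral t distribution with n − 1 degrees of freedom and noncentrality 0.968√n, gives 77.7% power at n = 10 and 82.4% at n = 11. The stated 11 is reproduced. With 15 randomised, power is 93.6%, and 15 − 11 = 4 children can be lost before n falls to 11.

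**The case against.** The strongest reply is that the article already deals with this. The retention sentence follows in the next paragraph and makes no exception for severe events. Section 3.9.1 says that every participant is assessed at the four time points. The severe-event sentence stands in the section on the intervention, so it can be read as a stopping rule for stimulation. The English is loose enough that the contrast between leaving the study and leaving the intervention may not be deliberate. The event is also known before the rule acts, because the physicians must first judge it severe, and a trained physician attends the sessions.

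Much of this stands. The benign reading is available, so a flat contradiction cannot be claimed. Identification of the event itself is not threatened; what is exposed is its later course and the remaining tests. But the benign reading has to be inferred, while the sentence as written points the other way. This is also a stated rule and not a detail left out for brevity, so an unseen full protocol or analysis plan does not excuse the wording.

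A reader might go further and infer that such a child drops out of the safety report or the analysis, that clinical care ends, or that the efficacy result is biased in a known direction. The article says none of this. It names no analysis set, and that may properly be left to the full protocol or analysis plan.

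**Conclusion.** The point holds as a minor inconsistency. A post-randomisation rule ties removal from the study to an event that belongs to the secondary aim, sits badly with the promise of data from discontinuers, and leaves open which governs. Its size per affected child is 3 of 4 neuropsychological assessments (event in cycle 1) or 1 of 4 (event in cycle 2), plus the later course of the event. These counts rest on the literal reading. The number of children affected cannot be estimated from the article. No loss of power and no direction of bias is claimed.

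**What to change.** In section 3.8, make a severe adverse event a reason to discontinue further stimulation in place of a reason for exclusion from the study. Add that the child is followed until the event resolves, and that the remaining scheduled assessments are sought under the existing sentence on participants who discontinue, subject to the right to withdraw.

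The cost is one or two sentences and a little more data to record. The four assessments are already scheduled. The gain is more complete safety follow-up and fewer data missing because of an outcome. It will not restore an active-sham contrast for a child stopped in cycle 1.
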